### Aims

The study involving acutely admitted older medical patients has three primary aims (1) to determine whether a medication review intervention is superior to standard care in improving medication appropriateness from admission to 8 weeks after discharge, (2) to determine the accuracy of eGFR equations based on various biomarkers compared to mGFR at a single-time point, and (3) to determine whether an individualized multimodal and transitional nutritional intervention is superior to standard care in improving the quality of life from admission and 16 weeks after discharge.

The study also has the following secondary aims which are related to the effect of the intervention: (1) to measure differences in polypharmacy, PIM use, and assessment of underutilization between the MED-intervention and standard care from admission to 8 weeks after discharge and (2) to measure of the differences in body weight, protein- and energy intake, mobility, cognition, frailty, the intestinal microbiome, and health care costs between the MULTI-NUT-MED intervention and standard care from admission to 8 and 16 weeks after discharge and 1 year after discharge (only health care costs).

Secondary aims, which are based on baseline data or data from the control group, include assessment of (1) how information from a broad pharmacogenetic test can potentially improve medication prescribing appropriateness; (2) how polypharmacy, PIMs, nutritional status, frailty, and inflammation modify the effect of the MED-intervention on prescribing appropriateness; (3) how non-GFR determinants affects eGFR and how the choice of eGFR equation affects medication prescribing; (4) how the choice of malnutrition classification criteria affects the prevalence of malnutrition; and (5) how different definitions of frailty affect the distribution of patients classified as frail or sub-frail as well as the responsiveness of these methods.

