**Fig. 2 Fig2:**
[figure not shown]
Schematic overview of the MULTI-NUT-MED and MED intervention elements and their timeframe. X indicates the timepoint of the intervention element. *These interventions are provided on an individually assessed need. Thus, only the possible timespan of the intervention is indicated. Abbreviations: Multidisciplinary (MULTI), Nutrition (NUT), Medication (MED), and Activities of Daily Living (ADL)

**Table 1 Tab1:** A schematic overview of the study design. Definition of timepoints: t_1_: Within 36 h after admission the ED, t_a_: Immediately after data collection upon enrollment has ended, t_GFR_: During hospitalization or up to 2 weeks after discharge, t_2_: 8 weeks after discharge, t_3_: 16 weeks after discharge, t_1y_: 1 year after discharge. Abbreviations: *GFR* glomerular filtration rate, *MULTI* multidisciplinary, *NUT* nutritional, *MED* medication

Timepoint	Enrollment	Allocation	Post allocation			Close-out
	t_1_	t_a_	t_GFR_	t_2_	t_3_	T_1y_

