**Confirmative outcomes**						
*Underutilization of medication*	x			x	x	
*Energy and protein intake*	During admission			x	x	
*Mobility*	x			x	x	
*Activities of daily living*	x			x	x	
*Well-being*	x			x	x	
*Frailty*	x			x	x	
*Anthropometry*	x			x	x	
*Blood pressure and heart rate*	x			x	x	
*Mortality*					x	x
*Cognition*	x			x	x	
*Depression*	x			x	x	
*Blood samples*	x		x	x	x	
*Health economy*	x				x	x

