Body composition	Total and segmented lean body mass and bone mineral content are measured with whole-body Dual-energy X-ray Absorptiometry (DXA) (GE Lunar Prodigy Primo, GE Healthcare Technologies, Madison, Wisconsin, US). DXA-scan is a clinical standard and validated to assess body composition [115]. Total and segmented body fat, fat-free mass, soft lean mass, bone mineral content, and intra- and extracellular water are measured using Bioelectrical Impedance Analysis (BIA) performed with InBody S10 [116]. Standardization, regarding fasting, physical activity, and urination prior to the measurement are not possible due to the acute setting. Information on these parameters is therefore collected prior to the measurement.	t_GFR_ During admission, t_1_, t_2_, t_3_ and t_GFR_
Blood pressure and heart rate	In a sitting, relaxed position blood pressure and heart rate are measured with a Microlife, BP A3L Comfort, automatic monitor, 3 times in a row on the right upper arm, with a break of 30 s in between measurements.	t_1_, t_2_, t_3_
Mortality	The Danish Register of causes of death [117] is a national registry where the cause of death noted in the medical evaluation after death is gathered.	t_1_, t_2_, t_3,_ t_1y_
Cognition	The trail making test [118] assesses the time it takes the participant to draw a line between 25 consecutive numbers that are scattered randomly on a piece of paper and are recorded. In the Digit Symbol Modalities test [119], the participant fills in as many as possible digits corresponding to a symbol in 90 s. The number of correctly filled in digits is recorded. In Hopkins Verbal Learning Test Revised [120], 12 words are read out loud, and the number of recalled words are recorded. Further, a list containing the 12 words and other words is read out loud, and the correctly and incorrectly recognized words are recorded. A delayed recall is of the 12 words is furthermore performed. The Mini-Mental State Examination [121] consists of 11 questions and tasks and provides a score between 0 and 30. The Orientation-Memory-Concentration test [122] consists of three questions concerning time and place, two tasks of concentration, and one task on memory.	t_2_, t_3_ t_2_, t_3_ t_2_, t_3_ t_2_, t_3_ t_1_, t_2_, t_3_
Depression	The Mini-Geriatric Depression Score [88] measures the need for medical evaluation of depression with 5 yes/no questions.	t_1_, t_2_, t_3_

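### The cognition aim runs from admission to 8 and 16 weeks, but four of the five cognitive tests have no admission value and the plan gives them no baseline-adjusted analysis

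*Protocol article*

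**What the plan says.** Under Aims, the second of the secondary aims on the effect of the intervention is "to measure of the differences in body weight, protein- and energy intake, mobility, cognition, frailty" and further outcomes, "between the MULTI-NUT-MED intervention and standard care from admission to 8 and 16 weeks after discharge".

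Table 1 has a single row for cognition, under the confirmative outcomes, marked at t1, t2 and t3. Its legend defines the first of these as "t_1_: Within 36 h after admission the ED"; t2 and t3 are 8 and 16 weeks after discharge.

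Table 2 (Outcomes) breaks the domain into five instruments: the trail making test, the Digit Symbol Modalities test, the Hopkins Verbal Learning Test Revised, the Mini-Mental State Examination (MMSE) and the OMC test. The time-point column for that row reads "t_2_, t_3_ t_2_, t_3_ t_2_, t_3_ t_2_, t_3_ t_1_, t_2_, t_3".

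Under Statistical methods, Secondary outcomes, cognition has no model of its own. It falls under the general rule for the remaining confirmative outcomes: t test, Kruskal-Wallis, chi-square, two-proportion z test or Friedman's analysis, chosen by distribution and adjusted for multiple testing. Missing secondary data are to be imputed in the way described for the primary outcomes, where the predictors are earlier measurements of the outcome being imputed, together with age, sex and other variables.

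**The concern.** Read in its ordinary sense, the aim asks how cognition develops from admission in each arm. That needs an admission value, and the schedule does not collect one for four of the five tests. No later analysis plan can supply it.

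Two consequences follow for those four tests. First, the default analysis uses no baseline information on cognition. Scores in older, acutely admitted patients can be expected to vary widely for reasons unrelated to the intervention, so precision is lost and a chance difference in cognition between the arms at entry goes unhandled, although a baseline cognitive score (OMC) is on file. Second, the imputation rule relies on earlier values of the same outcome, and at week 8 there are none.

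The article also does not say whether cognition is compared as a change or as a level at follow-up. For an outcome labelled confirmative, that choice should be settled before the data are seen.

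**Working it through.** The plan gives no figure for this point, so the check is a count, a comparison of sections and one short variance calculation.

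**1. Match tests to time points (Table 2, Cognition row).**

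| Test, in order of listing | Time points | Admission value |
|---|---|---|
| Trail making | t2, t3 | no |
| Digit Symbol Modalities | t2, t3 | no |
| Hopkins Verbal Learning Revised | t2, t3 | no |
| MMSE | t2, t3 | no |
| OMC | t1, t2, t3 | yes |

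Five tests line up with five entries. If the PDF reading had disturbed the order, four entries would still lack t1. Change from admission is estimable for 1 of 5 tests; 4 of 5 (80%) have follow-up values only.

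**2. Compare with Table 1.** The row covers the whole domain. Its t1 mark is met by OMC, so it is true but too coarse to show which test it refers to.

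**3. Compare with the analysis text.** The group tests listed for the remaining confirmative outcomes take no covariates. The adjusted regression models in the same paragraph are for associations between variables. By contrast, the article adjusts for the baseline value in its analyses of the Medication Appropriateness Index, EuroQol-5D-5L and the Shannon index.

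**4. Compare with the imputation rule.** For the four tests at t2, the earlier-measurement predictor is empty, which leaves age, sex and the other listed variables. At t3 the t2 score can serve, but only in participants who were tested at t2. Missing values are to be expected: Sample size assumes 25% dropout, and the minimal follow-up set under Data collection methods contains no cognitive test.

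**5. What adjustment for baseline OMC could gain.** Let r be the correlation between baseline OMC and a later test score. The document gives no value, so r = 0.4 to 0.6 is assumed. Residual variance as a share of the unadjusted variance is 1 − r².

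- r = 0.4: 1 − 0.16 = 0.84, a fall of 16%. Equivalent gain in sample size: 1/0.84 = 1.19, about 19%.
- r = 0.6: 1 − 0.36 = 0.64, a fall of 36%. Equivalent gain: 1/0.64 = 1.56, about 56%.

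Age and education could add to this; no figure is put on them.

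**The case against.** Several points on the other side stand.

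- **The tables do not conflict.** A reader might infer that Table 1 promises an admission value for every test and so contradicts Table 2. It does not: one row stands for the domain, and OMC satisfies the mark.
- **The aim does not use the word change.** The same sentence covers "differences in body weight, protein- and energy intake, mobility, cognition, frailty, the intestinal microbiome, and health care costs". Costs accumulate over a period and are not a change from an admission score, so the phrase could describe an observation window. Elsewhere, when the authors mean change from baseline, they say so. The change reading is therefore natural but not forced. Even under it, the aim names the domain, and OMC provides one admission-to-follow-up measure.
- **Week 8 is not declared a baseline.** A reader might infer that, with t2 the earliest value, the effect will be taken as the change from t2 to t3, which would show nothing of an effect reached by week 8 and held. The statistical section does mention mixed models and paired tests for repeated measurements, but nowhere does it make t2 a reference value or name a t2-to-t3 contrast as the cognition effect. That loss would come from a misuse the document does not state, and it is not counted here.
- **Validity is intact.** Allocation is randomized and stratified by age and sex, so follow-up scores can be compared between arms without bias. Leaving long tests out of the emergency department may well be deliberate and reasonable.
- **Some of the remedy is analysis-plan detail.** The choice of covariates for a non-primary outcome is often left to a plan that is not shown here.

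What these points do not remove is the mismatch between the aim and the instrument schedule, or the fact that the analysis and imputation rules the article does state do not suit four of the five tests.

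**Conclusion.** The concern holds in a limited form. The aim of comparing cognition from admission onwards can be met as change from admission for 1 of 5 tests only. For trail making, digit-symbol, Hopkins and MMSE, what can be estimated is a between-arm difference at 8 and 16 weeks. That comparison is unbiased, but the stated default leaves it unadjusted, and the stated imputation has no earlier value to draw on at week 8.

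The cost is in precision and clarity. It would be too strong to say that cognition cannot be analysed. No primary outcome or sample size is affected.

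The count rests on Table 2 alone and is secure. The 16 to 36% reduction in residual variance rests on an assumed correlation of 0.4 to 0.6. OMC is taken during acute illness and the four tests do not all measure what it measures, so the true correlation may lie below that range. The gain would then be smaller, but adjusting for one baseline score would still cost next to nothing.

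**What to change.** 1. In Aims or Outcomes, state that admission-to-follow-up change in cognition is assessed with the OMC test only.
2. For trail making, digit-symbol, Hopkins and MMSE, define the outcome as the between-arm difference in score at 8 and at 16 weeks. Estimate it by regression/ANCOVA or a mixed model adjusted for baseline OMC, age and education, in place of the unadjusted t-type or rank tests. Scores whose distribution does not suit a linear model can be transformed, or analysed with a model that suits them, using the same covariates.
3. Add baseline OMC to the imputation model for these four tests.
4. Footnote the Table 1 cognition row to say that the t1 mark refers to OMC.

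All three covariates are already collected at t1 (OMC in the Cognition row of Table 2, age and education among its descriptive variables), so no further testing in the emergency department is needed. The cost is a few sentences of text and a narrower claim: for four tests the trial will report a difference at follow-up, not a change from admission.

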#### Medication review intervention (MED intervention)

After the final medication list is obtained and baseline data are available, each participant is given a structured, patient-oriented medication review by the clinical pharmacist. All medications are reviewed to evaluate the (1) agreement with current national guidelines regarding choice of medication, dose, and dosing interval; (2) whether the goal of treatment has been met; (3) presence of nausea, constipation, diarrhea, loss of appetite, or dry mouth related to use of the medication; and (4) whether there is inadequate treatment of any current diagnoses or conditions. PIMs are identified using the Screening Tool of Older Persons’ Prescriptions criteria version 2 [64]. Prescribing recommendations based on eGFR are obtained from Renbase® [65] and “pro.medicin.dk,” a database containing information on national medication and treatment guidelines [66]. Medications are considered “renal risk medications” if dose adjustments are recommended at eGFR ≤90 mL/min/1.73 m^2^. Drug interactions are determined using the national database “interaktionsdatabasen.dk” [67]. Finally, each prescribed medication is assessed for appropriateness based on the indication for treatment, recommended dose, adverse drug reactions, therapeutic duplication, dosing interval, formulation and strength, drug interactions, contraindications, precautions, and specific participant characteristics. The clinical pharmacist documents any recommended changes to the participant’s medication list in the electronic patient record. These recommendations are then reviewed by a geriatrician, who decides whether to accept, reject, or alter each recommendation in collaboration with the clinical pharmacist. Any medication changes made by the geriatrician are documented, in the electronic patient record and implemented in the ED, accepted but not implemented in the ED, communicated to a specialized hospital ward and/or the participant’s GP, or rejected [36].

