#### Dietary counseling

Dietary counseling is provided both during hospitalization, by research dieticians, and after hospital discharge by community-based dieticians or by hospital-based research dieticians if community-based dieticians are not available. The goal of dietary counseling is to ensure that each participant receives a diet that covers the energy and protein requirements to either maintain their body weight (if BMI≥18.5) or gain body weight (if BMI <18.5). Both the content of the dietary counseling and the structure of the home visits after discharge are inspired by Lindegaard et al. [68, 69].

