#### Adherence

Recruitment, data collection, and interventions are all performed either in the hospital (during hospitalization) or in the participant’s home (after discharge). This strategy is performed to maximize patient recruitment, data collection, and compliance to the intervention while minimizing participant transportation costs and efforts. Adherence to the intervention is registered and evaluated but not monitored during the trial.

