Intestinal microbiome	All participants at risk of malnutrition or with malnutrition according to the nutritional screening tool MNA-SF will collect a fecal sample using EasySampler [129]. Samples collected during hospitalization are frozen as fast as possible at −80°. If collected in the home of the participant, the sample is frozen as fast as possible in the participants own −18° freezer for maximally 3 days. The samples are transferred in a cooler bag with freezer elements to the −80° freezer (Biobank). At the time of collection, the participant reports where the sample belongs on the Bristol Stool Scale [130] and their use of antibiotics.	t_1_, t_2_, t_3_
Blood samples	Blood samples are analyzed for: Alanine aminotransferase, albumin, basic phosphatase, bilirubin, carbon dioxide, C-reactive protein, hemoglobin, coagulation factors II, VII, and X International Normalized Ratio, potassium, urea, coagulation factors, leukocytes, neutrophils, mean corpuscular hemoglobin concentration, mean cell volume, sodium, platelets, lactate dehydrogenase, neutrophil gelatinase-associated lipocalin, BTP and B2M, soluble urokinase plasminogen activator receptor, cholesterols, triglycerides, blood sugar, glycated hemoglobin, insulin, markers of the effect, and plasma levels of medication. Calculation of eGFR will be based on the Chronic Kidney Disease Epidemiology Collaboration [131–133], Berlin Initiative Study [132], Full Age Spectrum [42, 134, 135], Lund-Malmö revised [136], the Caucasian and Asian pediatric and adult subjects [137], Modification of Diet in Renal Disease [138], and Cockcroft-Gault [42] equations based on creatinine, cystatin C, B2M or BTP, or a combination of the markers.	t_1_, t_2_, t_3_, t_GFR_
Health economics	Use of health care services will be collected from the following registries: National Patient Registry, National Health Insurance Registry, The Danish National Prescription Registry [139], and local databases in the municipalities.	t_1-_ t_3_ and t_1_-t_1y_
Descriptive variables	Participant characteristics are based on participant self-report or obtained from the medical journal and include sex, age, civil status, living conditions, education, smoking status, alcohol consumption, physical activity level, use of home- and health care, early warning score and diagnoses.	t_1_

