#### Secondary outcomes

The difference in health care costs between the control group and MULTI-NUT-MED intervention group will be evaluated in two stages. In the first stage, the share of participants having zero costs is compared by *t* test or similar. In the second stage, the magnitude of strictly positive health care costs is compared by generalized linear models [144]. Quality-adjusted life-years (QALYs) will be computed based on survival, EuroQol-5D-5L data collection, and Danish preference weights [145]. Incremental cost-effectiveness ratio (ICER) will be computed by dividing the difference in development in health care costs from inclusion to 52 weeks after inclusion between groups with the difference in change in QALYs between groups. The ICERs will be bootstrapped and reported with confidence limits from the bootstrapping, in scatter plots, and in cost-effectiveness acceptability curves.

The difference in AOU score change from baseline to 8 weeks after discharge between the control group and pooled intervention group (MED or MULTI-NUT-MED intervention) will be evaluated similarly to the difference in MAI score change.

DNA sequencing of fecal bacteria will be mapped to an integrated catalog of reference genes of the human gut microbiome in order to generate an operational taxonomic unit. Microbial species and gene diversity (the gut microbiome composition) will be calculated with the Shannon index. Differences in the Shannon index between the control group and intervention group will be evaluated by ANCOVA adjusted for baseline values. Gut microbiome diversity will be evaluated by descriptive analyses in relation to dietary components and nutritional status evaluated by MNA-SF and Global Leadership Initiative on Malnutrition (GLIM) criteria.

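### The stated cost sources and ICER formula include no term for delivering the intervention, so hospital-, research- and trial-supplied inputs count only if a registry happens to record them

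*Protocol article*

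**What the plan says.** The health economics row of Table 2 (Outcomes) names the data sources: "Use of health care services will be collected from the following registries: National Patient Registry, National Health Insurance Registry, The Danish National Prescription Registry", "and local databases in the municipalities". Data collection methods adds that registry data are obtained retrospectively.

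Under Statistical methods, Secondary outcomes, costs are compared between the control group and the MULTI-NUT-MED group in two stages. In the first, "the share of participants having zero costs is compared by" a t test or similar; in the second, positive costs are modelled. The ICER follows: "Incremental cost-effectiveness ratio (ICER) will be computed by dividing the difference in development in health care costs from inclusion to 52 weeks after inclusion", over the between-group difference in QALY change. It is bootstrapped and shown as scatter plots and acceptability curves. Neither place mentions an intervention cost, a staff-time record or a unit-price source.

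On delivery, each intervention participant receives a "structured, patient-oriented medication review by the clinical pharmacist", which a geriatrician then considers. Dietary counselling in hospital is given by research dieticians, and after discharge "by community-based dieticians or by hospital-based research dieticians if community-based dieticians are not available". On records of delivery, the Adherence section says: "Adherence to the intervention is registered and evaluated but not monitored during the trial".

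**The concern.** An ICER for a new service should charge the service to the arm that receives it. Here the article gives a list of sources and a formula, and neither contains such a charge. The inputs at issue go to one arm only, so any omission is one-sided: it lowers the incremental cost and cannot raise it. Bootstrapping describes sampling variation and does not remove a shift of this kind. A reported cost saving, or an ICER under a decision threshold, could then owe something to what was not counted. Health care costs are among the article's stated secondary aims, so the comparison will be reported.

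**Working it through.** The article states no cost, QALY or ICER figure, so there is nothing to reproduce. The check has three parts.

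**1. Which inputs the named sources could bring in**

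| Input (section) | Provider or supplier | Could a named source hold it? |
|---|---|---|
| Medication review (MED intervention) | Clinical pharmacist and geriatrician | Not stated; only if a hospital registry records it |
| In-hospital counselling (Dietary counseling) | Research dieticians | Not stated; same condition |
| Post-discharge diet visits, fallback (Dietary counseling) | Hospital-based research dieticians | Not stated; not municipal staff |
| Dysphagia evaluation in hospital (Occupational therapy) | Hospital occupational therapist | Not stated |
| Oral evaluation (Oral health-related intervention) | Research dentist; Setting says dentists are not normal hospital staff | Not stated |
| Hygienist home visits, two | Employer not given | Not stated |
| Electric toothbrush | Provided to participants | Not a service contact |
| Protein supplement P-Boost (Standard care; During hospitalization) | Intervention group only | Not a service contact |
| Post-discharge diet visits, dysphagia and ADL therapy, physiotherapy | Community-based staff by default | Plausibly, in municipal databases |
| Oral nutritional supplements after discharge | Prescription filled at a pharmacy | Plausibly, in the prescription registry |

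**2. How large the community part is**

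Maximum scheduled community contact for a participant who receives every element:

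- dietician: 4 visits × 1 h = 4 h
- dysphagia therapy: 2 h × 16 weeks = 32 h
- ADL therapy: up to 7 × 1 h = 7 h
- physiotherapy: 2 × about 1 h × 16 weeks = 32 h, or 2 × 13 = 26 h if it starts after the re-evaluation at week 3

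Total: 4 + 32 + 7 + 32 = 75 h, or 4 + 32 + 7 + 26 = 69 h. These are the hours that municipal databases may hold, so they do not measure the omission. Staff time for the hospital and research elements is not given; the article gives only the number of hygienist visits. The omitted share therefore cannot be computed.

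**3. Sensitivity of the ICER to any omitted amount**

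Let D be the omitted delivery cost per intervention participant and ΔQ the QALY gain. The true ICER is (recorded cost difference + D) / ΔQ, so omitting D lowers it by D / ΔQ.

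For ΔQ, take the planned EuroQol-5D-5L difference of 0.15 at 16 weeks (Sample size) and assume a linear rise from zero:

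- first 16 weeks: 0.15 × (16/52) / 2 = 0.023
- then held to week 52: 0.15 × 36/52 = 0.104, so ΔQ = 0.127
- or fading linearly to zero at week 52: 0.104 / 2 = 0.052, so ΔQ = 0.075

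With D = 1,000 currency units: 1,000 / 0.127 ≈ 7,900 per QALY, and 1,000 / 0.075 ≈ 13,300 per QALY. A smaller true gain makes the shift larger.

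**The case against.** The strongest reply is that this is a condensed article. It gives no unit prices, perspective or costing method for any item, and the full protocol or a health-economic plan may cost the intervention separately. Adherence is registered, so delivery data exist, and nothing bars their use. This stands as a limit on certainty: the documents do not prove that the final ICER will omit these costs. It does not remove the point, because the article goes beyond silence. It lists the sources and fixes the numerator, and following that text literally adds no delivery cost.

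A reader might infer that the registries hold none of the intervention. The documents do not support that. They never describe registry content, and the National Patient Registry could record some hospital contacts.

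A reader might also take the 69 to 75 scheduled hours as the omitted work. That is not supported either, since those hours are assigned by default to community staff. The research-dietician fallback is limited too: under the recruitment rules, patients from a municipality are not assessed for eligibility on days when its staff are insufficient for the later nutritional intervention.

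The zero-cost stage settles nothing. It might suggest that delivery is not counted, because counting it would leave almost no intervention participant at zero. But every participant is an acute inpatient at inclusion, so zero cost would be unusual in either arm if that stay is counted.

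**Conclusion.** The point holds in a limited form. The stated sources and formula do not bring in the hospital-, research- and trial-supplied inputs except where a registry happens to record them. The direction of any resulting bias is clear: the incremental cost is understated, in favour of the intervention. Its size is unknown, because the documents give neither unit costs, nor staff time for these elements, nor a description of what the databases hold. The figure of 7,900 to 13,300 per QALY for each 1,000 currency units omitted is an illustration. It rests on the planned 0.15 difference being achieved and on the assumed time courses. The point concerns a secondary health-economic endpoint and leaves the three primary outcomes untouched.

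**What to change.** In the health economics row of Table 2 and in the cost paragraph under Secondary outcomes:

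- Define the intervention-arm cost as registry and municipal service use plus the delivery cost of the hospital-, research- and trial-supplied elements.
- Build delivery cost from the adherence records (contacts per element, products supplied) at standard unit costs. Where those records lack minutes, state an assumed duration per contact.
- Exclude any contact already found in a registry or municipal database, so that nothing is counted twice.
- Use this total for the ICER numerator and the acceptability curves, and report the registry-only difference separately as downstream cost.

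The price is some costing work on data that the trial already registers, and probably a less favourable ICER. If an unseen health-economic plan already does this, one sentence in the article's cost paragraph closes the point.
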